### Outcomes

Primary and secondary outcomes are summarized in Table 2.

**Table 2 Tab2:** Overview of constructs and assessments throughout the randomized controlled pilot study protocol

Construct	Measurement	Description	Intervals assessed	Reference
Primary outcomes				
Feasibility of study		Number of eligible participants, randomized participants, retention and attrition of randomized participants	Baseline, mid-pregnancy, post-program, 3-month postpartum	[65]
Acceptability of IPT		IPT session attendance (≥ 80%), above-average participant IPT program ratings	Post-program	[66]
Secondary Outcomes				
Social functioning	SAS-SR	24-item self-report scale of interpersonal functioning in family, friend, romantic, and school or work domains	Baseline, mid-pregnancy, post-program, 3-month postpartum	[67]
	NRI-BSV	28-item self-report scale of relationship characteristics for mother, father, peer, and romantic partner relationships		[68]
Perceived stress	PSS	14-item self-report scale to assess perception of stress	Baseline, mid-pregnancy, post-program, 3-month postpartum	[69]
Depression	CES-D	20-item self-report scale to assess depression symptoms	Baseline, mid-pregnancy, post-program, 3-month postpartum	[70]
	EPDS	10-item self-report scale to assess depression symptoms	Baseline, mid-pregnancy, post-program, 3-month postpartum	[71, 72]
	MINI-KID	Structured clinical interview to assess psychiatric disorders, such as major depressive disorder	Baseline, post-program, 3-month postpartum	[73]
Disinhibited eating	EDE	Semi-structured interview to assess disordered eating including objective binge, subjective binge, and objective overeating	Baseline, post-program, 3-month postpartum	[74, 75]
	EES-C	25-item self-report questionnaire to assess eating in response to negative emotions	Baseline, mid-pregnancy, post-program, 3-month postpartum	[76]
Physical activity	ActiGraph GT3X+	Body-worn accelerometer to measure 7 days and nights of habitual physical activity including step counts, light and moderate-vigorous intensity, and sedentary time	Baseline, mid-pregnancy, post-program	[77, 78]
Sleep disturbance	ActiGraph GT3X+	Body-worn accelerometer to measure 7 nights of sleep including total sleep time, sleep onset latency, wake after sleep onset, and sleep efficiency	Baseline, mid-pregnancy, post-program	[79, 80]
Body composition	BMI indices	Height and weight measured to calculate BMI	Baseline, mid-pregnancy, post-program, 3-month postpartum	[81]
Maternal postpartum adiposity	Body fat	DXA conducted to measure body composition including total fat and lean mass	3-month postpartum	[82, 83]
Maternal insulin sensitivity	WBISI, QUICKI, HOMAIR	7-sample, 2-h oral glucose tolerance test to estimate insulin sensitivity	3-month postpartum	[84, 85]
Infant adiposity	Body fat	Infant PeaPod conducted to measure body composition including total fat and lean mass	3-month postpartum	[86]

*Baseline* baseline/screening assessment occurring around 12–18 weeks gestation; *Mid-Pregnancy* mid-pregnancy assessment occurring around 21–28 weeks gestation; *Post-Program* post-program assessment occurring around 30–34 weeks gestation; *3 Month Postpartum* assessment occurring around postpartum week 12; *SAS-SR* Social Adjustment Scale, Self-Report; *NRI-BSV* Network of Relationships Inventory-Behavioral Systems Version; *PSS* Perceived Stress Scale; *CES-D* Center for Epidemiologic Studies-Depression Scale; *EPDS* Edinburgh Postnatal Depression Scale; *MINI-KID* Mini-International Neuropsychiatric Interview for Children and Adolescents; *EDE* Eating Disorder Examination; *EES-C* Emotional Eating Scale-Adapted for Children; *BMI* body mass index (kg/m^2^, *z*-score, percentile); *DXA* dual-energy X-ray absorptiometry; *WBISI* whole body insulin sensitivity index; *QUICKI* quantitative insulin sensitivity check index; *HOMAIR* homeostasis model assessment of insulin resistance

#### Primary outcomes

##### Feasibility of study

Feasibility will be defined according to several metrics, including feasible recruitment, enrollment, and retention. Estimates are derived from previous longitudinal studies with pregnant women [65, 87–90]. Feasible recruitment will be defined as identifying at least 480 potentially eligible patients based upon medical record review by research staff to approach during the prenatal intake visit. Feasible enrollment will be defined as approximately 25% (120/480) of preliminary eligible patients agreeing to schedule a screening/baseline assessment and about 67% (80/120) attending the assessment and enrolling in the study. Feasible enrollment will be estimated as 60% (50/80) of enrolled patients being eligible to be randomized. Finally, feasible retention will be assessed as at least 75% (38/50) of randomized participants successfully completing at least three of four assessment intervals, including the baseline/screening assessment. This definition of feasible retention refers to the assessment intervals only and does not include the IPT sessions.

##### Acceptability of IPT

Acceptability will first be measured by IPT session attendance. Acceptable IPT session attendance will be defined by 50% of participants randomized to IPT attending 5 or 6 (≥ 80%) of the total 6 sessions [87–90]. Acceptability will also be measured by participant ratings on a program acceptability interview adapted for the current study from the Treatment Process Questionnaire and administered by a project staff at the end of treatment assessment [66]. This questionnaire asks participants to report on their reasons for enrolling in the study, what they liked and did not like about the IPT program and the perceived impact of the IPT program on their mood and health. Acceptable participant ratings will be defined as above-average ratings.

#### Secondary outcomes

##### Social functioning, perceived stress, and depression

Participants complete self-report questionnaires assessing social functioning, perceived stress, and depression on a computer through Research Electronic Data Capture (REDCap). A project staff member reviews completed questionnaires for missing items before the conclusion of the study visit and invites participants to respond to those missing items.

Social functioning is measured by two questionnaires. The Social Adjustment Scale-Self-Report (SAS-SR) is a 23-item questionnaire assessing social role functioning in several domains including peer, family, romantic relationships, and school/work [67]. Higher scores indicate worse social functioning. The Network of Relationships Inventory-Behavioral Systems Version (NRI-BSV) is a 28-item questionnaire assessing five social support features and three negative interaction features [68]. Stress is assessed as a continuous measure of stress perception by the Perceived Stress Scale (PSS), a 10-item questionnaire [69]. Higher scores suggest greater stress perception. Depression is measured by two questionnaires. The Center for Epidemiological Studies-Depression Scale (CES-D), a 20-item questionnaire assessing depression as a continuous measure of symptoms [70]. Depression is also assessed as a continuous measure of symptoms on the Edinburgh Postnatal Depression Scale (EPDS), a 10-item questionnaire [71, 72]. Higher scores on the CES-D and the EPDS are indicative of more elevated depression symptoms. Finally, depression diagnosis is assessed via the Mini-International Neuropsychiatric Interview for Children and Adolescents (MINI-KID), a structured diagnostic interview for psychiatric disorders in children and adolescents.

##### Eating behavior

The overeating section of the Eating Disorders Examination (EDE) Version 14.0, a semi-structured clinical interview [74, 75], is administered by trained research staff to assess overeating episodes with and without a feeling of subjective loss-of-control. The EDE has demonstrated good reliability and validity in adolescent samples [91]. Emotional eating, referring to eating in response to negative emotions, is assessed with the Emotional Eating Scale-Adapted for Children and Adolescents (EES-C) [76]. The EES-C is a 25-item self-report questionnaire that has shown good psychometric properties in adolescent samples [76].

##### Physical activity and sleep disturbance

Habitual physical activity, sedentary behavior, and sleep disturbance are derived from ActiGraph GT3X+ accelerometers (ActiGraph, Pensacola, FL), which have well-established validity and reliability in adolescents [77, 79]. These lightweight monitors are worn for seven days and nights on participants’ non-dominant wrist and are only removed for water-based activities, such as showering or swimming. Accelerometers record data with a sampling frequency of 30 Hz using 60-second epochs. Light physical activity, moderate-to-vigorous activity, and sedentary time are classified based on mean counts per epoch according to established guidelines [78]. Parameters of sleep disturbance include total sleep time, sleep onset latency, wake after sleep onset, and sleep efficiency [80].

##### Gestational weight gain

Weight is derived to the nearest 0.1 kg on a calibrated digital scale, and height is derived by a stadiometer in triplicate. Weight and height will also be derived from the medical record for intervals that do not coincide with a study assessment interval. More specifically, weight and height will be derived from the medical records at prenatal appointments, at delivery, and at postnatal appointments. Continuous GWG during pregnancy will be measured using two metrics: [1] GWG during the experimental phase, as defined by the difference between measured maternal weight at the baseline assessment to the post-program assessment, and [2] total GWG, as defined by the difference between self-reported pre-pregnancy weight and maternal weight at delivery, derived from the medical record. Classification of pre-pregnancy weight status as normal weight, overweight, or obese will be based on CDC BMI percentile for age [81]. Categorical GWG, defined as appropriate versus excessive, will be measured relative to Institute of Medicine guidelines for gestational age for both GWG during the experimental phase and total GWG.

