#### Post-program assessment

Participants complete an assessment at the end of the experimental phase, which corresponds to about 12–18 weeks after the baseline assessment and just prior to delivery. This assessment takes about two hours. Participants repeat the same research tasks as at the baseline assessment. In addition, a project staff member administers a program acceptability interview to adolescents who were randomized to the IPT condition. Participants are paid $75 for completing the post-program assessment.

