### Statistical analysis

Baseline participant characteristics and feasibility/acceptability findings will primarily be measured with descriptive statistics, including mean with standard deviation, median with interquartile range, frequency, and percentage. Analysis of covariance (ANCOVA) will be used to evaluate group differences (IPT + usual care versus usual care) in secondary outcomes, including social functioning, perceived stress, depression symptoms, eating behaviors, physical activity, sleep disturbance, maternal post-partum insulin sensitivity, maternal post-partum adiposity, and infant adiposity. We will use 95% confidence intervals to measure precision of the estimated differences between conditions, per recommendations [95]. Given that this is a pilot study, results will be considered preliminary. Although our theoretical framework suggests that IPT + usual care, as compared to usual care only, will impact these secondary outcomes via a series of mechanistic pathways, this pilot feasibility study is not sufficiently powered to test mediation. Covariates considered in these models will include baseline maternal age, gestational age, race/ethnicity, baseline CES-D score, and pre-pregnancy BMI/weight status. Missing data will be examined for patterns of missingness and imputation, with the intent-to-treat sample, will be used if deemed appropriate. Given the pilot nature of the study, we also will conduct sensitivity analyses using listwise deletion with complete data.

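### Experimental-phase weight gain is a raw kilogram difference, although elapsed time between the two weights can differ by 6 to 10 weeks across participants

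*Protocol article*

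**What the plan says.** The Gestational weight gain section defines two continuous metrics. The first is "GWG during the experimental phase, as defined by the difference between measured maternal weight at the baseline assessment to the post-program assessment". The second is "total GWG, as defined by the difference between self-reported pre-pregnancy weight and maternal weight at delivery, derived from the medical record". Both are plain subtractions. The categorical version is treated differently, for both periods: "Categorical GWG, defined as appropriate versus excessive, will be measured relative to Institute of Medicine guidelines for gestational age".

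The timing of the two experimental-phase weights is given in three places:

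- The Table 2 footnote has "baseline/screening assessment occurring around 12–18 weeks gestation" and "post-program assessment occurring around 30–34 weeks gestation".
- The Post-program assessment section describes the visit by time since baseline, "which corresponds to about 12–18 weeks after the baseline assessment and just prior to delivery".
- Table 3 puts the post-intervention measures, including weight, in the week-36 column.

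On adjustment, the Statistical analysis section says: "Covariates considered in these models will include baseline maternal age, gestational age, race/ethnicity, baseline CES-D score, and pre-pregnancy BMI/weight status". The time point of gestational age is not spelled out. Baseline is the natural reading, and the covariates are only under consideration.

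**The concern.** Weight rises through pregnancy, so a participant observed for longer gains more at the same rate. A raw difference mixes the rate of gain, which the intervention is meant to change, with time under observation, which it is not. The article recognises this for the categorical outcome by tying it to gestational age, but not for the continuous one, which carries more information with about 25 participants per arm.

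Two things are at stake. One is precision: spread in visit timing becomes avoidable spread in the outcome. The other is a route to bias: the post-program visit follows randomization, so if it falls later on average in one arm, that arm shows extra gain unrelated to treatment. Later visits in the IPT arm would work against IPT; earlier visits would flatter it.

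**Working it through.** **Interval between the two weights.** Shortest = earliest post-program week minus latest baseline week. Longest = latest post-program week minus earliest baseline week. Baseline is at weeks 12–18 throughout.

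- Table 2 footnote (weeks 30–34): 30 − 18 = 12 to 34 − 12 = 22 weeks, a spread of 10.
- Post-program assessment section: 12 to 18 weeks as stated, a spread of 6. The Table 2 windows reproduce this only if every post-program visit is at week 30 (30 − 18 = 12; 30 − 12 = 18). Counted from a baseline at weeks 12–18, it would put the visit anywhere from 12 + 12 = 24 to 18 + 18 = 36 weeks.
- Table 3 (week 36): 36 − 18 = 18 to 36 − 12 = 24 weeks, a spread of 6.

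The three statements do not agree.

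**Assumptions for size.** The article gives no weekly gain and no SD. I take 0.3–0.6 kg/week, a residual SD of 4–6 kg, visit timing uniform and independent within the Table 2 windows, and 25 per arm (Sample size section).

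**Between individuals.** The difference between the longest and shortest intervals is 10 × 0.3 to 10 × 0.6 = 3–6 kg, or 6 × 0.3 to 6 × 0.6 = 1.8–3.6 kg on a 6-week spread. These are extremes for single participants, not arm differences.

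**Noise.**

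- SD of the interval = √((6² + 4²)/12) = 2.08 weeks.
- Variance inflation = 1 + (rate × 2.08)²/SD². At 0.3 kg/week and SD 6 it is 1.011; at 0.6 kg/week and SD 4 it is 1.097. That is about 1–10%.
- SE of the chance arm difference in mean interval = 2.08 × √(2/25) = 0.59 weeks, so the 95% range is ±1.15 weeks, or ±0.35 to ±0.69 kg.
- For comparison, the 95% CI half-width for the arm difference is 1.96 × SD × √(2/25) = 2.2 kg (SD 4) to 3.3 kg (SD 6).

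**What baseline gestational age removes.** With the Table 2 windows, the post-program share of the timing variance is 16/(36 + 16) = 31%. After adjustment the remaining timing SD is 4/√12 = 1.15 weeks. The inflation falls to (0.3 × 1.15)²/6² = 0.3% at the low end and (0.6 × 1.15)²/4² = 3.0% at the high end. If every visit were at one fixed week, the covariate would account for all of the linear timing effect.

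**Bias if post-program timing differs by arm.** Bias = weeks of difference × rate, so one week gives 0.3–0.6 kg. With m = bias/(SD × √(2/25)), the two-sided 5% test rejects with probability Φ(m − 1.96) + Φ(−m − 1.96). For 0.3–0.5 kg/week:

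| Arm difference in timing | Bias (kg) | Rejection rate with no true effect |
|---|---|---|
| 1 week | 0.3–0.5 | 5.4–7.3% |
| 2 weeks | 0.6–1.0 | 6.4–14.3% |
| 4 weeks | 1.2–2.0 | 10.9–42.4% |

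Four weeks is the full width of the Table 2 window, so the last row needs one arm entirely at week 30 and the other entirely at week 34.

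**The case against.** The strongest reply is that nothing in the article shows visit timing differing by arm. The post-program visit is defined by gestational week or by weeks since baseline, identically for both arms, and the IPT section has sessions finished by 28–30 weeks, before the 30–34 week window opens. This stands: a reader might infer that timing differences will appear as treatment effects, and the document does not support that.

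Arm-related drift is nonetheless plausible. Staff are not blinded, only one arm has a session schedule, and the acceptability interview is given at this visit to IPT participants only. Six sessions at 2–3 week spacing take 5 × 2 = 10 to 5 × 3 = 15 weeks, so a participant starting at week 18 on the wider spacing would finish at week 33. Table 3 shows sessions at weeks 24–34, which does not match the IPT section; those passages need reconciling.

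Other replies also hold:

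- Randomization is at the end of the baseline visit. Baseline week, and the gain before it that total weight gain includes, are balanced in expectation. They add noise or chance imbalance, not systematic bias.
- Total weight gain is a defensible quantity as defined. Delivery outcomes are themselves in the secondary aim, and IPT could affect delivery week, so scaling by it would condition on a possible effect of treatment.
- A missed post-program visit need not lose the endpoint, because chart weights are collected and imputation is foreseen.
- The categorical outcome already refers to gestational age, weight gain is a secondary outcome, and the results are declared preliminary.
- The list of ANCOVA outcomes is open-ended, so not naming weight gain there is no fault in a condensed article.

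None of this answers the narrower point: the second weight's timing is left in the experimental-phase metric when dates that would remove it are available.

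**Conclusion.** The point holds for experimental-phase continuous weight gain only. A raw difference over an interval with a 6- to 10-week spread is a weaker measure than one that uses the elapsed time, and a baseline gestational-age covariate repairs it only in part.

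The certain cost is small: about 1–10% variance inflation without adjustment, and about 0.3–3% with baseline gestational age adjusted, under the assumed rates, SDs and uniform Table 2 timing. The conditional cost is a bias of about 0.3–0.6 kg for each week by which post-program timing differs between arms. One week is small beside a CI half-width of 2.2–3.3 kg; several weeks would not be. Whether any such difference will occur cannot be told from the article.

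This is a cheap improvement to a secondary outcome, not a threat to the pilot's primary aims. Separately, the three statements of post-program timing conflict whatever analysis is chosen.

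**What to change.** 1. Analyse experimental-phase weight gain as kg per week between the two dated weights. Alternatively, fit a mixed model to the study weights and prenatal chart weights available in both arms, with gestational week as the time axis and the arm-by-week slope as the effect. Leave out weights taken at IPT sessions, which only one arm has.
2. Reconcile the post-program timing in the Table 2 footnote, Table 3 and the Post-program assessment section, so that the interval defining the outcome is stated once.
3. Keep total weight gain as defined. A version referenced to gestational age at delivery is optional, as a sensitivity analysis.

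This changes wording and analysis only; the weights are already to be collected, and their dates come with the visits. Kilograms per week is a slightly less intuitive unit than kilograms, and it removes only the linear part of the timing effect. The mixed model can allow for a changing rate at the price of more specification.

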##### Maternal postpartum weight retention

Continuous maternal postpartum weight retention will be measured as the difference in self-reported pre-pregnancy weight and measured maternal weight at the 3-month postpartum assessment [39].

##### Maternal postpartum adiposity

For those who participate in the adjunct metabolic assessments, participants have a dual energy X-ray absorptiometry (DXA) scan to evaluate body composition, including total lean mass and total fat mass, using Hologic QDR Discovery A (S/N81337; Bedford, MA) [82]. DXA has demonstrated good validity in youth [83].

##### Maternal postpartum insulin sensitivity

Maternal insulin sensitivity is derived from a 2-hour oral glucose tolerance test at the 3-month postpartum interval. In the morning following a 10-hour overnight fast, participants ingest 1.75 g/kg of glucola (max = 75 g). Blood is sampled via an intravenous line for insulin, glucose, and c-peptide at fasting, 10, 20, 30, 60, 90, and 120 min after ingesting the glucola [85]. Insulin sensitivity will be estimated with the whole body insulin sensitivity index (WBISI), as well as the quantitative insulin sensitivity check index (QUICKI) and the homeostasis model assessment of insulin resistance (HOMA-IR). These methods of measuring insulin sensitivity have been validated against euglycemic-hyperinsulinemic clamp-derived measures in youth with overweight and obesity [84].

##### Infant adiposity

At the 3-month postpartum assessment, infants will complete a PEAPOD to evaluate fat mass and fat-free mass using air displacement plethysmography [86].

### Participant timeline

All assessments take place at the CAMP clinic, with the exception of the 3-month postpartum assessment, which takes place at the Outpatient Pediatric CTRC at Children’s Hospital Colorado. Participant timeline is presented in Table 3.

**Table 3 Tab3:** Overview of a participant’s timeline, assessment intervals, and core measures

	Study Period											
	Initiation of prenatal care	Allocation	Intervention						Post-intervention			3-month post-partum
**Gestational week**		12–18	24	26	28	30	32	34	36	38	40	
Enrollment												
Eligibility Screen	X											
Informed Consent		X										
Allocation		X										
Interventions												
IPT			X	X	X	X	X	X				
UC												
Medical	X	X	X	X	X	X	X	X	X	X	X	X
Nutrition	X			X								
Social work	X			X					X			
Assessments												
Feasibility	X	X	X	X	X	X	X	X	X			X
Acceptability	X	X	X	X	X	X	X	X	X			
Social functioning		X			X				X			X
Perceived stress		X			X				X			X
Depression	X	X	X	X	X	X	X	X	X			X
Eating behavior		X			X				X			X
Physical activity		X			X				X			
Sleep disturbance		X			X				X			
Height/weight	X	X	X	X	X	X	X	X	X	X		X
Maternal insulin sensitivity												X
Maternal adiposity												X
Infant adiposity												X

*IPT* interpersonal psychotherapy, *UC* usual care

